##### Implementation costs

Efficiency is defined as the ratios between implementation cost and service uptake, and implementation cost and degree of normalization. Within the ImpleMentAll study, implementation costs are defined as the sum of personnel costs, other direct costs, and indirect costs. Personnel costs are calculated by multiplying the working hours spent by the implementers on implementing the iCBT service by standardized hourly wage rates and a standardized country correction factor. Other direct costs include costs for consumables, equipment, and services purchased for the purpose of carrying out the implementation activities. Indirect costs are costs that cannot be attributed directly to the implementation work but are necessary to facilitate the implementation, such as office rent, office IT infrastructure, or administration. Indirect costs are calculated by taking 20% of the direct costs. Implementation costs (i.e. personnel costs, other direct costs, and indirect costs) will be assessed in the local implementation settings by monitoring the different cost components over time.

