**Fig. 5 Fig5:**
[figure not shown]
Three-step iterative working process for each module to reach consensus among relevant stakeholders

In order to engage with stakeholders throughout the process, a number of consensus techniques are recommended, including brainstorming, structured group discussions, individual and informal discussions, and surveying [28]. Surveying functionalities are embedded within the *ItFits-toolkit* to allow implementers to flexibly create dedicated online surveys which they can administer to relevant stakeholders via email. In addition, the toolkit allows implementers to upload and store notes, audio recordings, and other relevant materials, which document the decisions and progress made and can be used for reviewing purposes. Implementers are also actively working with evidence-informed materials, including literature on iCBT relevant determinants of practice [23, 37, 38] and implementation strategies [25, 26, 39], as well as guidelines to develop and structure the tailored implementation plan [40].

The commitment of study sites to participate in the trial and to use the toolkit according to the study protocol has been agreed in advance, and resources have been allocated to support their participation. Each participating site is required to work with the toolkit for at least 6 months and is instructed to strive to finish all four modules within this time period. The intensity of use depends on the local context and needs. For the toolkit, a protocolized introductory training will be provided, and periodic support (in form of monthly support sessions and assistance on request) will be available, focusing solely on technical questions, such as login procedures, the use of tools, or the navigation through the platform, to ensure a smooth working process without interfering with the working components of the toolkit. Within the toolkit itself, there is access to written, audio, and video guidance to completing activities within the modules. The training and support will be provided by two members of the research team.

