### Statistical methods

For the normalization outcomes, a three-level GLMM will be conducted, with ‘Wave’ clustered at the ‘Staff’ level, and ‘Staff’ clustered at the ‘Site’ level, accounting for the correlation structure in the outcome. Random effects will be used to assess correlations between observations within and across units in the same clusters. Each regression parameter, including the intercept, will be allowed to vary within cluster levels ‘Staff’ and ‘Site’. Efficiency of the implementation process (i.e. normalization and service uptake divided by implementation costs) will be included in the separate analyses.

It will be tested whether the introduction of the *ItFits-toolkit* influences iCBT service uptake by patients across and within sites [55, 56]. An effect of the toolkit is demonstrated when service uptake shows a significant main effect of *ItFits-toolkit* use or an interaction effect of *ItFits-toolkit* use and measurement wave (time). Consequently, trial data will be analysed using generalized linear mixed modelling (GLMM) [55] with service uptake as the dependent variable, and measurement wave (time), *ItFits-toolkit* use (yes/no), and interaction between time and *ItFits-toolkit* use as independent variables. To account for the expected intervention lag effect, a fractional term for the ‘*ItFits*’ parameter will be included in the 6-month minimal exposure time (ranging from 0 to 1, i.e. 0–½–1). Service uptake outcomes will be modelled in a two-level GLMM, since these measures are collected at the site level only. Thus, to account for the correlation structure of the uptake outcome, ‘Wave’ is modelled to be clustered at the ‘Site’ level. All regression parameters will be allowed to vary.

For exploratory purposes, measures of exposure to the *ItFits-toolkit* (event-based log files showing intensity of use and level of continuous use), CSQ, SUS, and ORIC questionnaire data will be added as additional predictors of outcome in the above-described regression models.

In the analyses, all observed data will be included following the intention-to-treat principle. The ability of mixed models to estimate model parameters in the presence of missing observations will be used, and increased uncertainty caused by missing values will be accepted as a given quality of the results.

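### Efficiency is not given one orientation across the article, and its cost side omits the research team's training and support, which exist only under the toolkit

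*Protocol article*

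**What the plan says.** The protocol article defines efficiency under Methods, Exploratory outcomes, Implementation costs: "Efficiency is defined as the ratios between implementation cost and service uptake, and implementation cost and degree of normalization". Under Statistical methods it returns to the same quantity: "Efficiency of the implementation process (i.e. normalization and service uptake divided by implementation costs) will be included in the separate analyses".

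The cost side is built from three parts, all under Implementation costs and all assessed in the local settings:

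- Personnel: "Personnel costs are calculated by multiplying the working hours spent by the implementers on implementing the iCBT service by standardized hourly wage rates", with a country correction factor.
- Purchases: "Other direct costs include costs for consumables, equipment, and services purchased for the purpose of carrying out the implementation activities".
- Overhead: "Indirect costs are calculated by taking 20% of the direct costs".

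The description of the experimental condition makes the implementers a core team of up to four people per site. It also describes an introductory training, monthly support sessions and help on request, and says who delivers them: "The training and support will be provided by two members of the research team".

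**The concern.** There are two separate problems.

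**Orientation.** The outcomes section lists cost first and leaves the numerator open. The statistics section puts cost in the denominator. If the analysis works with one ratio per site and wave, the choice is more than a matter of presentation, because the mean of a ratio is not the reciprocal of the mean of its inverse. An open choice could also be settled after the data are seen.

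**Scope of cost.** As described, the research team's training and support are neither implementers' hours nor a purchased service, so the formula has no place for them. They arise only once a site has the toolkit. Leaving them out lowers recorded cost in the toolkit condition and nowhere else. The Discussion says the toolkit will be made available if effective, and an organization deciding whether to adopt it would want to know what that support costs.

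**Working it through.** **What can be reproduced.** The article gives no cost, uptake or efficiency figure, so there is no planned number to rebuild on this point. The staff sample size does reproduce (15/0.80 = 18.75, rounded up to 19; 19 × 12 = 228; 228 × 10 = 2280) but has no bearing here.

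**Step 1: orientation.** All inputs are assumed and serve only to show what can happen. Take two site-waves per condition, each costing 10. Completers are 10 and 10 under usual implementation, 4 and 20 under the toolkit.

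| Summary | Usual implementation | Toolkit | Toolkit looks |
|---|---|---|---|
| Mean of cost/uptake | (1 + 1)/2 = 1.00 | (2.5 + 0.5)/2 = 1.50 | worse |
| Mean of uptake/cost | (1 + 1)/2 = 1.00 | (0.4 + 2.0)/2 = 1.20 | better |
| Total cost/total uptake | 20/20 = 1.00 | 20/24 = 0.833 | better |
| Total uptake/total cost | 20/20 = 1.00 | 24/20 = 1.20 | better |

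Averaged ratios reverse the verdict; ratios of totals do not. Inversion by itself changes only the sign of the contrast. The reversal needs uneven ratios that are averaged or modelled on their raw scale.

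**Step 2: zero counts.** Service uptake is an absolute number of completers, collected every three months per site. With cost C > 0 and no completers in a wave, C/0 is undefined, while 0/C = 0.

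**Step 3: omitted support.** Let D be the recorded direct cost of a toolkit period and X the direct value of the research team's training and support. With 20% overhead the formula records 1.2D; counting support would give 1.2(D + X). The omitted share is therefore f = 1.2X/1.2D = X/D, and recorded outcome per cost is too high by the factor 1 + f.

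If the recorded figures show an efficiency gain g for the toolkit, the change after counting support is (1 + g)/(1 + f) − 1:

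| Apparent gain g | f = 5% | f = 10% | f = 20% | f = 30% |
|---|---|---|---|---|
| 10% | +4.8% | 0% | −8.3% | −15.4% |
| 20% | +14.3% | +9.1% | 0% | −7.7% |

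The sign reverses only when f exceeds g. The values of f and g are assumed, since the documents supply neither.

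**The case against.** The strongest reply is that the two sections do not contradict each other. A ratio between two quantities names no numerator, and "normalization and service uptake divided by implementation costs" is the only explicit form, so a reader should simply use it. Under that form a wave without completers gives zero, not an undefined value. Costs are assessed locally, so leaving out help supplied by the research team is a legitimate site perspective. That help is purely technical, and implementers' own hours on the toolkit appear to be counted. Ratio modelling and zero handling may also be left to an analysis plan.

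Much of this stands. It makes the first problem a mismatch of order, not a pair of opposing formulas. It does not remove the need for one wording in both places. On cost, a site perspective is defensible once declared, but the article does not say that research-provided support is excluded.

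Some stronger readings are tempting and are not supported:

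- *Consulted stakeholders' uncounted hours also favour the toolkit.* Consultation is central to the toolkit, but usual implementation includes training deliverers and educating staff, which also takes uncounted time outside the core team. The net direction is not established.
- *At least 12 trainings and 72 support sessions go uncosted.* The product 12 sites × 6 months = 72 assumes separate sessions at every site, all taken up. The sessions are only said to be available, and the Discussion describes batch-wise training; with two sites per sequence, six trainings would fit.
- *Cost per NoMAD point mostly tracks cost.* Setting a 5% change in NoMAD against a 20% change in cost compares unequal inputs, and the article gives no variance for either.

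**Conclusion.** The point holds in a limited form. The article does not give efficiency one orientation throughout, and if site-wave ratios are analysed on the raw scale the two orientations can lead to different verdicts. The example (1.50 against 1.00, and 1.20 against 1.00) shows that this is possible, not that it is likely in this trial. A reader might infer that inverting the ratio by itself changes which condition is more efficient; for a single unit or a ratio of totals it does not.

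The firmer part is the cost formula. As written, it leaves out a resource used only in the toolkit condition, so recorded toolkit efficiency is inflated by 1 + f. The direction is clear for this item if support has any cost. The size cannot be computed from the documents, and the conclusion would reverse only if f exceeded the apparent gain. Efficiency is an exploratory outcome, and the primary NoMAD comparison does not depend on it.

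**What to change.** 1. Use one definition in both sections. Preferably, model cost and outcome separately with the same stepped-wedge model, and report incremental cost alongside incremental completions and the change in NoMAD. This avoids site-wave ratios and the zero-count problem.
2. State the cost perspective and say explicitly whether support from the research team is inside it.
3. Report the efficiency comparison twice: without and with the research team's training and support hours, priced at the same standardized wage rates.
4. If stakeholder hours are collected, collect them in both conditions; costing them in toolkit periods alone would create a bias against the toolkit. Otherwise state that they are excluded. If waves have already passed, the item would be missing mainly from control periods, which argues for declaring the exclusion.

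The cost is some added analysis, a record of the research team's own hours, and a toolkit cost figure that becomes slightly less favourable. Nothing changes in the design or the primary analysis.

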##### Exposure

Exposure to the *ItFits-toolkit* will serve as a measure to determine if the measured change in outcomes can reliably be related to the use of the toolkit. Usage data will be automatically collected by system logs recording time stamped starting and stopping of *ItFits*-modules (use) and a binary confirmation of the existence of output of the modules (result).

##### Satisfaction

As the *ItFits-toolkit* is a newly developed tool*,* satisfaction of use will be assessed to establish to what extent the toolkit is able to fulfil implementers’ needs and expectations in tailored implementation. Satisfaction will be assessed with the short version of the Client Satisfaction Questionnaire (CSQ-3) [45], which has good psychometric properties and has been tested in numerous studies and diverse samples [46, 47].

##### Usability

Usability will be measured with the validated System Usability Scale (SUS) [48, 49]. The instrument measures the perceived, local usability of the *ItFits-toolkit*—such as complexity of the tool, user experience, and perception of the technological realization—by the toolkit user.

##### Impact

The perceived impact will be assessed to explore whether the implementation strategies developed by using the *ItFits-toolkit* are considered to be satisfactory in fulfilling the implementers’ needs. The perceived impact will be measured using a visual analogue scale.

##### Organizational readiness

Organizational readiness for implementing change [50, 51] is hypothesized to be a potential precursor or contextual factor for implementation success [52]. This concept will be assessed using the ‘Organizational Readiness for Implementing Change’ (ORIC) questionnaire [51], which focuses on the psychological and behavioural preparedness of members of an organization to implement organizational change [51]. Considering similarities in theoretical concepts, ORIC questionnaire data will also be used to explore its convergent validity with the NoMAD instrument.

Table 2 summarizes the primary and exploratory outcomes. All staff-level questionnaires have been translated and adapted into local languages using a standardized translation guide. The translated versions of the instruments are available for public use [53].

**Table 2 Tab2:** Primary and exploratory outcomes of the ImpleMentAll study

	Outcome	Instrument	Organizational level	Staff level
*Primary outcome*	*Degree of normalization*	NoMAD (20 items)	–	Baseline, 3-monthly
*Exploratory outcome*	*Demographics*	Self-developed questionnaire	Once during the study period	Baseline
	*Service uptake*	Self-developed questionnaire Data source: administrative data basis (e.g. iCBT platform)	Baseline, 3-monthly	–
	*Implementation costs*	Self-developed questionnaire Data source: financial administration	Baseline, 3-monthly	–
	*Exposure*	Event-based platform log-files	Continuous	–
	*Satisfaction*	CSQ (3 items)	End of exposure time	–
	*Usability*	SUS (10 items)	End of exposure time	–
	*Perceived impact*	Visual analogue scale (1 item)	End of exposure time	–
	*Organizational Readiness*	ORIC (12 items)	–	Baseline, 3-monthly

Outcomes, assessment instruments, the level on which the outcomes are assessed, and measurements’ time intervals. All staff-level questionnaires have been translated and adapted into local languages using a standardized translation guide

### Data collection

Data will be collected on implementation sites and staff level through (1) a central data management system specifically built for the purpose of the study and (2) event-based log files of the *ItFits-toolkit*. Online surveys will automatically be sent to participants via email with the request to fill in a specified measure. The measurement time points are pre-scheduled for 3-month intervals during the 30-month study period. Data on demographics are collected once, when a participant enters the study. Degree of normalization, uptake, implementation costs, and organizational readiness for change will be measured at 3-monthly intervals. Exposure data will be collected continuously, and data on satisfaction and usability will be recorded at the end of the exposure period (see Table 2). Depending on the participant’s activity, reminders will be sent at regular intervals to ensure continuous completion of the questionnaires by each participant. The burden for study participants to provide the required data is kept to a minimum by using brief online questionnaires and automatically collected data.

### Sample size and power estimates

This study has a fixed cluster sample size by design (*n* = 12 implementation sites) based on availability and willingness of organizations engaged in implementation of iCBT services to conform to the study’s eligibility criteria. For the staff-level outcome, a series of simulation studies was conducted using a multi-level degree of normalization data (i.e. NoMAD items) to estimate the minimal required number of staff members to sufficiently power the analysis. Here, a 5% increase in absolute normalization scores and an increased 3-month growth rate from .05 to .10 are assumed to be statistically decisive in superiority for either condition. The cluster sample size of 12 clusters, with 15 staff participants per implementation site per measurement wave, achieves > 80% power to detect this effect, using a two-sided test with a significance level *α* of .05. Taking a conservative study drop-out of 20% into account, the minimum staff sample size was set to *n* = 19 per implementation site. In line with the closed cohort design, each participant will be measured continuously over a period of 10 measurement waves. For all 12 clusters, this results in a total minimum sample size of 228 staff participants with 2280 repeated data points.

### Randomization

Implementation sites will be randomly allocated to one of six groups (two implementation sites per group, see Fig. 3) prior to the start of the study. Randomization will be conducted by a computerized random number generator using R [54]. No constraints to randomization will be applied. The allocation scheme can only be accessed by the central trial coordination team. Any other investigators and all study participants within the implementation sites will be blinded to the crossover sequence. Three months prior to cross-over, the two clusters randomized for rollout, the process evaluation team and the team involved in supportive activities of these sites, will be informed in order to prepare any organizational prerequisites necessary for using the *ItFits-toolkit*.

### Statistical methods

For the normalization outcomes, a three-level GLMM will be conducted, with ‘Wave’ clustered at the ‘Staff’ level, and ‘Staff’ clustered at the ‘Site’ level, accounting for the correlation structure in the outcome. Random effects will be used to assess correlations between observations within and across units in the same clusters. Each regression parameter, including the intercept, will be allowed to vary within cluster levels ‘Staff’ and ‘Site’. Efficiency of the implementation process (i.e. normalization and service uptake divided by implementation costs) will be included in the separate analyses.

It will be tested whether the introduction of the *ItFits-toolkit* influences iCBT service uptake by patients across and within sites [55, 56]. An effect of the toolkit is demonstrated when service uptake shows a significant main effect of *ItFits-toolkit* use or an interaction effect of *ItFits-toolkit* use and measurement wave (time). Consequently, trial data will be analysed using generalized linear mixed modelling (GLMM) [55] with service uptake as the dependent variable, and measurement wave (time), *ItFits-toolkit* use (yes/no), and interaction between time and *ItFits-toolkit* use as independent variables. To account for the expected intervention lag effect, a fractional term for the ‘*ItFits*’ parameter will be included in the 6-month minimal exposure time (ranging from 0 to 1, i.e. 0–½–1). Service uptake outcomes will be modelled in a two-level GLMM, since these measures are collected at the site level only. Thus, to account for the correlation structure of the uptake outcome, ‘Wave’ is modelled to be clustered at the ‘Site’ level. All regression parameters will be allowed to vary.

For exploratory purposes, measures of exposure to the *ItFits-toolkit* (event-based log files showing intensity of use and level of continuous use), CSQ, SUS, and ORIC questionnaire data will be added as additional predictors of outcome in the above-described regression models.

In the analyses, all observed data will be included following the intention-to-treat principle. The ability of mixed models to estimate model parameters in the presence of missing observations will be used, and increased uncertainty caused by missing values will be accepted as a given quality of the results.

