**Methods:**

A stepped wedge cluster randomized controlled trial (SWT) design will be applied. Over a trial period of 30 months, the *ItFits-toolkit* will be introduced sequentially in twelve routine mental health care organizations in primary and specialist care across nine countries in Europe and Australia. Repeated measures are applied to assess change over time in the outcome variables. The effectiveness of the *ItFits-toolkit* will be assessed in terms of the degree of normalization of the use of the iCBT services. Several exploratory outcomes including uptake of the iCBT services will be measured to feed the interpretation of the primary outcome. Data will be collected via a centralized data collection system and analysed using generalized linear mixed modelling. A qualitative process evaluation of routine implementation activities and the use of the *ItFits-toolkit* will be conducted within this study.

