#### Exploratory outcomes

##### Service uptake

Service uptake is defined in terms of the completion rate of the iCBT service, that is, the absolute number of patients actually completing the trajectory of the iCBT service during the trial period. Each implementation site has their own protocolized or experience-based operationalization of ‘completion’ according to the therapeutic principles and procedures of the local service being implemented. In addition to collecting data on completion rates, also data on referral rates will be collected to investigate the effect of the *ItFits-toolkit* on iCBT service uptake by staff, i.e. referral to the service.

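### For the exploratory service-uptake outcome, the either/or rule for a demonstrated toolkit effect has a false-positive rate of about 6–10% if each term is tested at 5%

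*Protocol article*

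**What the plan says.** The rule stands in the Statistical methods section: "An effect of the toolkit is demonstrated when service uptake shows a significant main effect of *ItFits-toolkit* use or an interaction effect" of toolkit use and measurement wave. The model behind it contains measurement wave, toolkit use (yes/no) and the "interaction between time and *ItFits-toolkit* use as independent variables". Both tested coefficients therefore come from one fit. During the six-month minimum exposure the toolkit term takes a fractional value, on the scale 0, ½, 1.

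Two other places bear on the rule:

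- **Status of uptake.** The abstract says: "Several exploratory outcomes including uptake of the iCBT services will be measured to feed the interpretation of the primary outcome". The Outcomes section and Table 2 also list uptake as exploratory. Its definition is in terms of patients who complete the iCBT service.
- **Significance level.** The article gives a level once, in Sample size and power estimates: "using a two-sided test with a significance level *α* of .05". That paragraph concerns normalization (NoMAD): "For the staff-level outcome, a series of simulation studies was conducted using a multi-level degree of normalization data". No level is given for uptake.

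**The concern.** A rule that declares success when either of two 5% tests is significant is not a 5% rule. Its error rate lies between 5% (the tests always agree) and 10% (they never reject together). Where it falls depends on the correlation between the two estimates.

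That correlation depends in turn on how wave is numbered. With the interaction in the model, the main effect is the toolkit effect at the wave coded zero. If T0 is coded zero, this is an effect at a wave when no site has the toolkit, since T0 to T2 are control data in every site. Moving the origin changes the quantity that the main-effect test addresses, and so changes the error rate of the rule, although data and fitted model stay the same.

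At stake is the reading of the uptake result. A result announced as a demonstrated effect would carry a weaker guarantee than a reader would assume.

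**Working it through.** **The plan's own figures.** The article states no error rate for the uptake rule, so there is none to reproduce. Its sample-size arithmetic does reproduce: 15 / (1 − 0.20) = 18.75, rounded up to 19 per site; 19 × 12 = 228; 228 × 10 = 2280. Those figures concern NoMAD and do not enter below.

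**Inputs from the article.** 12 sites in six sequences of two; ten waves, T0–T9; first cross-over at T2, then two sites every three months; T0–T2 solely control data; toolkit coded yes/no or 0–½–1; model terms wave, toolkit and their interaction.

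**Assumed, because the article does not give them.** Two-sided .05 for each uptake test; linear or categorical wave; the origin of time; a random site intercept with variance 0 or 1 and a random slope with variance 0, 0.05 or 0.2, relative to residual variance 1; normally distributed estimates with valid standard errors.

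**Step 1: limits.**
- Independent tests: 1 − 0.95² = 0.0975.
- Upper bound for any correlation: 0.05 + 0.05 = 0.10.

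**Step 2: union probability at correlation ρ.** The rate is 1 − P(|Z₁| < 1.96 and |Z₂| < 1.96) for a standard bivariate normal.

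| ρ | rate at .05 each | rate at .025 each |
|---|---|---|
| 0 | 9.75% | 4.94% |
| −0.45 | 9.21% | 4.71% |
| −0.85 | 7.46% | 3.84% |
| −0.90 | 7.04% | 3.62% |
| −0.97 | 6.13% | 3.13% |

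**Step 3: ρ in this design.** Let X be the 120-row design matrix and V the assumed covariance. The covariance of the estimates is (X′V⁻¹X)⁻¹, and ρ is read from the entries for toolkit and toolkit × wave. Feeding ρ into step 2 gives:

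| Wave in the model | Time origin | False-positive rate |
|---|---|---|
| Linear | waves numbered from 0 or 1 | 6.6–7.6% |
| Linear | centred (mid-trial or wave 6) | 8.8–9.75% |
| Categorical, linear interaction | waves numbered from 0 or 1 | about 6–6.6% |
| Categorical, linear interaction | centred at mid-trial | 8.3–9.5% |

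With uncentred linear wave ρ is about −0.83 to −0.94. With uncentred categorical wave it is about −0.94 to −0.98. Every coding tried gives more than 5%.

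**The case against.** **Uptake is exploratory.** Exploratory outcomes are commonly tested without multiplicity control. This stands, and it limits the weight of the point. It does not remove the point, because the article does not describe the uptake result in exploratory terms: it says when an effect is demonstrated.

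**No 5% is promised for uptake.** This also stands. The .05 belongs to the NoMAD power statement. Using it for each uptake test is the usual reading of *significant*, but it remains an assumption.

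**A condensed article may leave the alpha split to a fuller plan.** The absence of an adjustment is indeed no finding. The printed either/or criterion is a stated rule, however, and a fuller plan that followed it literally would inherit the error rate.

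**The excess is small.** With waves numbered as labelled and linear time it is about two percentage points. The upper end needs centred time, which the article does not state.

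A reader might go further in four directions. The article supports none of them.

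- **The primary test also exceeds 5%.** The planning effect has a level and a growth component: "a 5% increase in absolute normalization scores and an increased 3-month growth rate from .05 to .10 are assumed". But the article joins them with *and*, describes a single two-sided test, and writes no either/or rule for NoMAD.
- **The power is overstated.** The claim that the design "achieves > 80% power to detect this effect" would be affected only if the simulation counted either component as success. Nothing says it did.
- **Release of the toolkit hangs on this rule.** Release is conditional on effectiveness, and the article expresses effectiveness through the degree of normalization. A false positive on uptake would not by itself meet that condition.
- **Referrals add further chances.** The article says "also data on referral rates will be collected to investigate the effect of the *ItFits-toolkit* on iCBT service uptake by staff". It defines uptake by completions, however, collects referrals in addition, and introduces the rule for uptake by patients.

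**Conclusion.** The point holds for service uptake alone. As printed, the rule lets either of two correlated tests establish a toolkit effect. At .05 per test its false-positive rate is about 6–10%, depending on whether wave is linear or categorical and where time is set to zero. The article fixes neither.

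The range rests on a normal approximation on the scale of the linear predictor, on assumed variance structures, and on standard errors that are otherwise valid with 12 sites. Any small-sample inflation would come on top and is not counted here.

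This is a modest defect in a stated decision rule for an exploratory outcome. It is worth correcting because the wording claims more than the rule can support, and because the error rate should not depend on how the waves are numbered. It is no evidence of a fault in the primary analysis.

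**What to change.** In Statistical methods, replace the either/or sentence for uptake, measured by completions as the Outcomes section defines it, with one of these:

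1. A joint 2-df test of the toolkit and toolkit × wave terms at 5%. Its nominal level is 5% and its result does not change with the origin of time.
2. One prespecified contrast, such as the mean toolkit effect over the exposed waves, at 5%.

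Under either choice, show the two coefficients separately as description with confidence intervals, and state how wave is coded.

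Splitting the level at .025 per term would also keep the rate below 5% (4.94% if independent, about 3.6% at ρ = −0.9). It is conservative at the correlations expected here and still depends on the time origin, so it is the weaker choice.

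If no confirmatory claim on uptake is intended, the alternative is to drop *demonstrated* and label the uptake result exploratory.

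The cost is one sentence and, under options 1 and 2, a slightly higher bar for claiming an uptake effect. Data collection does not change.
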